### Data Capture and Outcomes

As per the registry protocol, there are no prespecified assessments or medical treatments to be performed other than a follow-up telephone call at 90 days (plus an additional 20 days if needed for administerial reasons) after the start of CytoSorb treatment. Data collection is performed based on medical chart review and transcription of deidentified data collected from hospital admission through discharge. The following key parameters are included (Textbox 3).

Data from the following time points will be collected if available (Textbox 4).

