### Analysis and Statistical Methods

Descriptive statistics and patient data listings will be used to summarize the data. Continuous variables will be summarized by nonmissing values (n), mean and SD (in case of normal distribution), median, 25th and 75th percentiles (in case of nonnormal distribution), and minimum and maximum. Categorical variables will be summarized by frequencies and percentages. Stratification of descriptive categories within treatment groups may occur if such elaborations are thought to be useful. Inferential statistical tests may be used, as appropriate, with an α critical value of .05 to indicate statistical significance. Inferential statistical tests will be 2-sided, unless specified otherwise. Also, 95% CIs may be used to compare event rates to a historical and clinically meaningful standard or to investigate the course of biomarkers (or certain laboratory values) after CytoSorb therapy. Multivariate analysis may be used to determine independent predictors of study outcomes. Missing data is unavoidable for critically ill patients treated in the intensive care unit (ICU). The principle of analyses is to only include the nonmissing observations. For inflammatory biomarkers or laboratory values that are highly associated with the use of hemoadsorption devices, sensitivity analyses will be performed by applying a multiple imputation method under the missing-at-random assumption.

Unless specified otherwise, minimum and maximum will be displayed to the same level of precision as the observed value. Mean and median will be displayed to 1 level of precision greater than the observed value. The SD and SE will be displayed to 2 levels of precision greater than the observed value. All *P* values will be rounded to and displayed as 3 decimals. If a *P* value less than .001 occurs, it will be shown in tables as <.001.

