## Results

The COSMOS registry is an international registry executed in countries where the device is approved and routinely used in everyday clinical practice. It started with the inclusion of the first patient on July 15, 2022. There is no prespecified sample size for the registry, but the current estimation is that with annual enrollment of approximately 300 patients, the registry can reach up to 3000 patients in 10 years. The COSMOS registry is now actively enrolling in 4 countries (Germany, Spain, Portugal, and Italy), with plans to expand to other countries outside of Europe. As of August 1, 2024, a total of 199 patients are included in the registry.

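### The missing-data rule does not separate death from a missing value, so before/after changes describe patients who survived to be measured, and SOFA, PELOD-2 and vasopressor outcomes have no stated sensitivity analysis

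*Protocol article*

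**What the plan says.** The rule stands in the protocol article under Analysis and Statistical Methods: "The principle of analyses is to only include the nonmissing observations". One exception follows. "For inflammatory biomarkers or laboratory values that are highly associated with the use of hemoadsorption devices", the article says that "sensitivity analyses will be performed by applying a multiple imputation method under the missing-at-random assumption". No other sensitivity analysis is named, and the sentence does not mention organ-dysfunction scores or vasopressors.

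The key-parameter list under Data Capture and Outcomes includes changes in SOFA (PELOD-2 in children), changes in inflammatory biomarkers, and vasopressor type, dose and duration. The data time points include the 24 hours before therapy, the therapy itself, and up to 24 hours after it. The same section says that "Data from the following time points will be collected if available" and that, apart from the day-90 telephone call, "there are no prespecified assessments or medical treatments to be performed".

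ICU, in-hospital and 90-day mortality are listed separately, as are vital status and registry exit date. Nothing in the article says how a death before the post-therapy value enters a change analysis.

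**The concern.** A pre- to post-therapy change needs a value after therapy. A patient who dies first has none, and under the stated rule leaves that summary without being marked as different from a patient whose sample was simply not ordered. The article describes its main indications as carrying high mortality, so the number who leave this way may not be small.

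MAR imputation is not designed for this. It predicts an unobserved value from patients with similar observed data. For a patient who has died there is no value to predict. In living patients, measurement follows clinical decisions, so whether a value exists may itself carry information about the patient's state, and no departure from MAR is examined.

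The abstract lists biomarker change, vasopressor requirements and organ function among the key outcomes, and the registry is meant to inform patient selection, timing and dosing. Tests are allowed "with an α critical value of .05 to indicate statistical significance", and confidence intervals may be used for the course of biomarkers after therapy. With no control group, nothing within the registry would show how much of an apparent improvement comes from losing the patients who died.

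**Working it through.** The document gives no death rate, effect size or responder definition for this point, and "There is no prespecified sample size for the registry". There is no figure of the plan's to reproduce. The steps below show mechanism and direction on assumed inputs.

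**Step 1. Mean change.** Let *d* be the share who die before the post-therapy value. The mean over all patients is (1 − *d*) × (mean in measured) + *d* × (mean in deceased). Therefore

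measured-only mean − all-patient mean = *d* × (mean in measured − mean in deceased).

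The second mean is notional, because those values never existed. Assume *d* = 5% to 30% and a change 2 to 6 SOFA points worse in the deceased. The overstatement of improvement runs from 0.05 × 2 = 0.1 to 0.30 × 6 = 1.8 points. With no gap it is 0, and with a gap in the other direction the sign reverses.

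**Step 2. Does MAR imputation correct it?** Simulation of 400,000 patients. All inputs are assumed: pre-therapy SOFA mean 12, SD 3; post-therapy SOFA = 12 + 0.6 × (pre − 12) + residual with SD 3; log-odds of death 0.4 per SOFA point; death the only cause of missingness. True mean change is about 0 (0.01). A single regression imputation stands in for the average result of multiple imputation. SOFA is used for its familiar scale; the plan's own imputation would apply only to biomarkers and laboratory values.

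Mean change (negative = improvement):

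| Early deaths *d* | Death follows post-therapy SOFA: measured only | same: MAR imputation | Death follows pre-therapy SOFA only: measured only | same: MAR imputation |
|---|---|---|---|---|
| 5% | −0.12 | −0.16 | +0.07 | 0.01 |
| 10% | −0.22 | −0.30 | +0.13 | 0.01 |
| 20% | −0.42 | −0.58 | +0.24 | 0.01 |
| 30% | −0.61 | −0.85 | +0.35 | 0.01 |

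When death follows deterioration, measured-only analysis shows an improvement that is not there, and MAR imputation shows a larger one. When death depends only on pre-therapy severity, measured-only analysis understates improvement and MAR imputation recovers the truth.

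**Step 3. Share improved.** In the same simulation, the share improving by at least 2 points at *d* = 20% is:

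- death follows post-therapy SOFA: 30.5% of measured patients, 24.4% of all treated with death counted as not improved;
- death follows pre-therapy SOFA: 24.2% and 19.3%.

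The second figure is lower under both mechanisms, because the share alive and improved among all treated is always the share improved among those measured × (1 − *d*) when death is the only reason for a missing value.

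**Step 4. Simple illustration.** With an assumed 60% improved among those measured:

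- *d* = 10%: 0.60 × 0.90 = 54%, a difference of 6 points
- *d* = 20%: 0.60 × 0.80 = 48%, a difference of 12 points
- *d* = 30%: 0.60 × 0.70 = 42%, a difference of 18 points

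**Step 5. Coverage of the sensitivity analysis.** Setting its scope beside the key-parameter list: inflammatory biomarkers and some laboratory values are covered; SOFA, PELOD-2 and vasopressor requirements are not.

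**The case against.** The strongest reply is that this is a condensed article about a mainly descriptive, single-arm registry. Rules for death before measurement are commonly left to the analysis plan, which the article mentions and which is not shown. Change in a biomarker among living patients is also a legitimate question, especially where removal of a substance is the aim. Both points have weight. They do not dispose of the matter, because the article states a general principle and one named check, and as stated these do not answer how deaths are treated.

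Several stronger readings are tempting, and the document does not support them:

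- **Deaths disappear from the registry.** They do not. Mortality is collected and listed as a key outcome, and the nonmissing count is to be reported for continuous variables. Values during therapy are also collected, so a patient who dies on treatment may contribute some data. What is lost is the patient's place in a change that needs a post-therapy value.
- **Patients who died will be given imputed values.** The text does not say so. It sets no restriction to living patients, but a rule imputing only while alive would be compatible with it.
- **MAR imputation is the check for all of these outcomes.** Its stated scope leaves out SOFA, PELOD-2 and vasopressors.
- **Both analyses must err favourably.** Step 2 shows that for mean change this depends on the death mechanism.
- **The plan overstates improvement by 12 points.** The document defines no responder endpoint, and the 60% and the death shares are assumptions. The 6 to 18 points are the gap between two different quantities, one among measured patients and one among all treated, and not an estimated bias.

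**Conclusion.** The point holds in a limited form. The stated rule yields before/after changes for patients who survived to be measured, without labelling them so. These will probably look too favourable as a description of everyone treated. That is likely rather than certain for mean change, since it rests on death tending to follow deterioration. A share improved among measured patients will exceed the share alive and improved among all treated whenever anyone who would otherwise be counted dies before the post-therapy value. The one named sensitivity analysis does not correct the bias when death follows deterioration, and it leaves out SOFA, PELOD-2 and vasopressors.

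The size cannot be computed from the document. The range of 0.1 to 1.8 SOFA points, the simulated figures, and the fall from 60% to between 54% and 42% all rest on assumed inputs. An analysis plan that is not shown may already settle part of this. The change is a worthwhile, cheap improvement to the analysis text.

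**What to change.** 1. Label change results as conditional on being alive and measured, and show beside each the number who died before the post-therapy value.
2. For SOFA, PELOD-2 and vasopressor requirements, add an analysis in all treated patients that counts death before the post-therapy value as not improved, either as the share alive and improved or by giving death the worst rank. Doing the same for every biomarker is a matter of preference and is not asked for here.
3. State that imputation applies only to values missing while the patient was alive.
4. Add a delta-adjusted, not-at-random sensitivity analysis for the biomarkers, and extend sensitivity analyses to SOFA and vasopressors.

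No new data are needed, because vital status and registry exit date are already collected. The cost is some analysis wording and a few extra tables. The improvement figures will be less favourable than those from measured patients alone.

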## Results

The COSMOS registry is an international registry executed in countries where the device is approved and routinely used in everyday clinical practice. It started with the inclusion of the first patient on July 15, 2022. There is no prespecified sample size for the registry, but the current estimation is that with annual enrollment of approximately 300 patients, the registry can reach up to 3000 patients in 10 years. The COSMOS registry is now actively enrolling in 4 countries (Germany, Spain, Portugal, and Italy), with plans to expand to other countries outside of Europe. As of August 1, 2024, a total of 199 patients are included in the registry.

## Discussion

### Overview

The previous CytoSorb international registry collected patient data from May 2015 to December 2020 and was independently led as an investigator-initiated project by the Centre for Clinical Studies at the Jena University Hospital, Germany [24]. At its closure, 46 sites had included a total of 1434 patients showing improvements in cardiovascular and pulmonary Sequential Organ Failure Assessment scores and a reduction in procalcitonin, C-reactive protein, and interleukin-6 levels [24]. However, several important parameters were not captured, for example, lactate and hemodynamic data, due to a lack of knowledge of hemoadsorption treatment characteristics at the time of conceptualization of the project. Also, the definition of sepsis and septic shock changed in 2016 [25]. Furthermore, other indications for blood purification, including bilirubin and myoglobin removal, were not yet covered at the time by the Conformité Européenne label and were therefore not considered in the initial design of the Jena registry.

Existing literature in the field of CytoSorb treatment mainly consists of smaller studies, case series, and case reports [16], including studies that showed neutral or negative results [17-19]. In the following paragraphs, we summarize the current understanding of the pathophysiology and rationale behind the most common use of CytoSorb in critically ill patients. Of note, so far, evidence is still scarce with a lack of larger RCTs in the field. In general, pooled analysis of such heterogenous patient groups is difficult, especially given the methodological limitations of these studies [26].

### Septic and Vasoplegic Shock

The clinical conditions of sepsis and septic shock arise from a dysregulated host reaction to an infection, causing organ malfunction. The excessive release of inflammatory mediators beyond the local area in response to the infection characterizes the syndrome, leading to an overshooting inflammatory response from the host (known as a cytokine storm). However, comprehension of the fundamental pathophysiology behind organ and especially vascular dysfunction, including inadequate vascular response to vasoconstrictors (vasoplegia) caused by sepsis, remains incomplete. Existing data support the concept of sepsis-associated cytokine release as the driving force in refractory vasoplegic shock [27,28]. Both sepsis and septic shock represent 2 of the main causes of death in ICUs worldwide [29,30]. This considerable mortality is at least in part attributable to the inadequacy of current treatment options. The only causal therapeutic options are comprised of infectious source control and antibiotic therapy, while stabilization of the cardiac and respiratory systems is considered supportive measures. However, there are several reasons why CytoSorb therapy might be able to provide benefits for critically ill patients in the ICU who develop severe organ dysfunction due to a dysregulated immune response (ie, often termed as “hyperinflammation” and “cytokine storm”). Existing clinical data on the use of CytoSorb hemoadsorption in patients with sepsis support the concept that a reduction in inflammatory mediators, but certainly also of other, yet unknown substances, can result in improved hemodynamics, reduced needs for catecholamines, reversal of shock, and improved outcomes [31-33]. The effect of hemoadsorption therapy on mortality as a primary end point has not yet been evaluated in a prospective randomized manner, but retrospective studies suggest significant survival benefits in the CytoSorb-treated group compared to matched controls [34,35]. Next to sepsis, vasoplegic shock also occurs in the context of noninfectious triggers such as polytrauma, severe burns, severe acute pancreatitis, and cardiogenic shock [29,36]. Additionally, vasoplegic shock is commonly seen postoperatively after cardiac and other major surgeries [37,38]. Patients with postoperative vasoplegia will be included in this registry; however, intraoperative use of the device during cardiac surgery will not be included. The separate STAR (Safe and Timely Antithrombotic Removal) registry is dedicated for the indication of intraoperative antithrombotic removal with CytoSorb hemoadsorption (NCT04976530).

### ARDS and ECMO

ARDS is characterized by bilateral interstitial edema of the lungs, resulting from increased capillary leakage. If the condition advances to severe ARDS, one sole lifesaving option available is frequently ECMO. Nevertheless, this approach is expensive, burdensome, and exceedingly invasive, requiring specialized personnel, and is typically only available in specialized facilities. It is crucial to note that the application of ECMO itself may exacerbate the underlying hyperinflammatory state [39]. Recent reports also suggest that patients treated for severe ARDS who received blood purification treatment show improvements in oxygenation, as evidenced by an increased partial pressure of oxygen to fraction of inspired oxygen ratio [40-44].

### COVID-19

Based on the emerging knowledge that hyperinflammation may play a key role in respiratory failure in patients with COVID-19, CytoSorb therapy has been used in this setting with over 7500 patients treated worldwide (as of December 2021), including the United States under Food and Drug Administration–issued emergency use authorization [45-49]. The recently released results from the multicenter US CytoSorb therapy in COVID-19 registry showed high survival in the most critically ill patients requiring life support on ECMO [43,50]. The same rationale for using CytoSorb in COVID-19 also applies to other viral infectious etiologies leading to severe respiratory failure, such as dengue fever or influenza [51-55].

### Liver Failure

Currently, the medical world fundamentally distinguishes between acute liver failure (including hyperacute or fulminant) and acute-on-chronic liver failure, but all types of liver failure are associated with very high mortality irrespective of the presence of preexisting liver disease [56,57]. For most patients, the only definitive treatment is liver transplantation, but availability is limited. Several artificial liver support systems have been used with the aim of bridging by detoxification in patients with liver failure [56]. CytoSorb has been shown to be effective for the removal of bilirubin [12,58,59] and bile acids [60,61].

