**Methods:**

The international COSMOS registry is collecting prospective data for patients treated with CytoSorb during routine care in various critical care indications, based on the decision of the treating physicians. Data are collected at baseline, during CytoSorb therapy, 24 hours thereafter, at discharge from the intensive care unit and the hospital, and on day 90. Key outcomes assessed include change in inflammatory biomarkers, vasopressor requirements, fluid balance, organ function and organ support, length of intensive care unit and hospital stay, occurrence of adverse events, and mortality.

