A recent randomized controlled trial (RCT) in healthy volunteers provided definitive mechanistic evidence of CytoSorb’s ability to decrease systemic cytokine levels after intravenous administration of endotoxin in an established sepsis model [11]. These findings support the approved indications of CytoSorb therapy for the treatment of a variety of clinical conditions in which excessively high plasma levels of inflammatory mediators occur, such as septic or vasoplegic shock, acute respiratory distress syndrome (ARDS), and critical illness requiring extracorporeal membrane oxygenation (ECMO) therapy. Additional application fields for CytoSorb include use of the device for removal of elevated levels of bilirubin and myoglobin in patients with life-threatening conditions, such as liver failure [12] or rhabdomyolysis [13], as well as the intraoperative removal of ticagrelor and rivaroxaban during cardiothoracic operations with cardiopulmonary bypass [14].

Despite the increasing worldwide use of blood purification therapies, large international, multicenter studies and robust evidence of clinical outcome improvement are still lacking [15,16]. Consequently, questions about the appropriate application modalities, especially regarding timing and dose, remain unanswered. Also, some conflicting data showing neutral or even negative outcomes have been published, underlining the need for further conclusive evidence generation [17-19]. A recent systematic review showed no mortality benefit of the therapy in a very heterogenic patient group and underlined the need to systematically identify patients likely to respond to the therapy with clinical benefits in a reproducible manner [16].

The hemoadsorption device can be easily integrated into concomitant continuous renal replacement therapy or into a dedicated hemoperfusion circuit (Figure 1), as well as into a bypass within the ECMO circuit or a cardiopulmonary bypass circuit.

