Key parameters.DemographicsBaseline characteristics including Acute Physiology And Chronic Health Evaluation II score, respective Pediatric Index of Mortality-3 score for children, and Charlson Comorbidity Index scoreIndication for CytoSorb treatmentDetails on the extracorporeal circuit used (eg, type of platform, blood flow rate, and anticoagulation regimen), integration of CytoSorb, and duration of treatmentChanges in Sequential Organ Failure Assessment scores or subscores and Pediatric Logistic Organ Dysfunction-2 score for childrenChanges in inflammatory biomarkers (C-reactive protein, procalcitonin, leukocytes, interleukin-6, and other interleukins)Laboratory results from hematology, chemistry, coagulation, and arterial blood gas analysis as well as additional drug level measurementsDuration of organ support therapies (number of days on extracorporeal membrane oxygenation or extracorporeal life support system, number of days on continuous renal replacement therapy, number of days on mechanical ventilation, and number of days on concomitant procedures like therapeutic plasma exchange)Daily fluid balanceVasopressor requirements (type, dose, and duration)Ventilation parametersLiver disease assessment (eg, hepatic encephalopathy, bilirubin, bile acids, model for end-stage liver disease score, respective pediatric end-stage liver disease score for children, European Association for the Study of Liver—Chronic Liver Failure score, Maddrey score, and Lille score)Acute kidney injury assessment, including Kidney Disease Improving Global Outcomes severity score and myoglobin and creatine kinase levels for rhabdomyolysisCritical illness polyneuropathyCumulative blood productsConcomitant therapies including plasmapheresis and medicationLength of intensive care unit (ICU) and hospital stayICU and in-hospital mortalitySafety performance of CytoSorb device, including collection of any unexpected serious adverse device effectsCases of device deficiencyLong-term follow-up on day 90 (+20) including 90-day mortality and cause of deathStudy exit: vital status and registry exit date

Data collected.Baseline (at intensive care unit [ICU] admission)Before start of CytoSorb therapy (maximum 24 hours prior)During CytoSorb therapyAfter CytoSorb therapy (maximum 24 hours afterward)At discharge from ICUAt discharge from hospitalFollow-up on day 90 (+20)

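### Early change in total SOFA is followed as organ function although the device removes bilirubin, the sole item of the SOFA hepatic subscore

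*Protocol article*

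**What the plan says.** All references are to the protocol article.

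- **Device effect.** The Liver Failure section of the Discussion states that "CytoSorb has been shown to be effective for the removal of bilirubin", and says the same of bile acids. Background and Rationale lists among the application fields "use of the device for removal of elevated levels of bilirubin and myoglobin in patients with life-threatening conditions".
- **Outcome.** The Methods paragraph of the Abstract includes among the key outcomes "organ function and organ support, length of intensive care unit and hospital stay, occurrence of adverse events, and mortality".
- **Measurement.** Textbox 3 in Data Capture and Outcomes lists change in SOFA, as total score or subscores. A separate item, liver disease assessment, covers "hepatic encephalopathy, bilirubin, bile acids, model for end-stage liver disease score" and further scores, ending with "Maddrey score, and Lille score". That item is not worded as a change.
- **Timing.** Textbox 4 lists ICU admission, the 24 hours before therapy, during therapy, the 24 hours after therapy, ICU discharge, hospital discharge and day 90.
- **Analysis.** Analysis and Statistical Methods allows 95% confidence intervals "to investigate the course of biomarkers (or certain laboratory values) after CytoSorb therapy" and multivariate analysis for predictors of outcome. It singles out "laboratory values that are highly associated with the use of hemoadsorption devices", but only to choose variables for a multiple-imputation sensitivity analysis.

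**The concern.** A score shows organ function only if treatment reaches it through the organ. Here the device acts on one of the score's inputs. While the adsorber runs, and for some time after, a lower bilirubin may mean better hepatic clearance, extraction by the cartridge, or both, and the hepatic subscore cannot tell these apart. Total SOFA inherits the problem.

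A control group would not remove it, because the device changes the measurement itself. The registry has no control group in any case.

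More is at stake than a descriptive table. The Objectives section wants to identify the patients who benefit most, and the Abstract's Conclusions name patient selection, timing and dosing. If SOFA change defines response, patients whose bilirubin lies just above a SOFA cut-off can be counted as responders, and more intensive adsorption can look more effective, with no organ having changed.

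**Working it through.** **Step 1: passages side by side.** The device lowers bilirubin (Background and Rationale; Liver Failure). Organ function is a key outcome (Abstract). SOFA change is collected (Textbox 3) during therapy and within 24 hours after it (Textbox 4). The one outside fact needed is the standard definition of the SOFA hepatic subscore: bilirubin only, with cut-offs at 1.2, 2, 6 and 12 mg/dL. Nothing in Analysis and Statistical Methods separates removed analytes from measures of function. The only acknowledgement of device-linked laboratory values concerns missing data.

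**Step 2: is there a figure to reproduce?** No. The article gives no bilirubin distribution, removal fraction or target SOFA change. What follows is illustration under stated assumptions.

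**Step 3: formula.** Assume lognormal bilirubin with median *m* and log-SD 0.6, and a net proportional reduction *r* at the post-therapy sample, with every organ unchanged. A patient loses one point for each cut-off *c* that lies below the true value and at or above the reduced value. The mean fall is therefore

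Σ over *c* of { Φ[(ln(*c*/(1−*r*)) − ln *m*)/0.6] − Φ[(ln *c* − ln *m*)/0.6] }.

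**Step 4: numbers.** Contributions are listed in the order of the cut-offs 1.2, 2, 6 and 12 mg/dL.

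| Median (mg/dL) | Net removal | Contributions by cut-off | Mean SOFA fall |
|---|---|---|---|
| 0.8 | 10% | 0.052 + 0.019 + 0 + 0 | 0.07 |
| 0.8 | 30% | 0.148 + 0.046 + 0 + 0 | 0.19 |
| 0.8 | 50% | 0.216 + 0.060 + 0 + 0 | 0.28 |
| 3 | 50% | 0.292 + 0.435 + 0.114 + 0.010 | 0.85 |
| 20 | 30% | 0.000 + 0.001 + 0.057 + 0.201 | 0.26 |

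Across medians of 3, 6, 12 and 20 mg/dL and removals of 30, 40 and 50%, the mean fall runs from 0.26 (median 20, 30%) to 0.85 (median 3, 50%). Simulation of the same model gives the same means. The share of patients whose hepatic subscore falls by at least one point ranges from 26% to 79% in these jaundiced scenarios. At median 3 mg/dL with only 10% removal, the mean fall is 0.12.

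**Step 5: reading.** The direction is fixed by the mechanism. The size depends on two quantities that the article does not give.

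**The case against.** The case on the other side has several parts, and much of it stands.

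- **No stated misreading.** A reader might infer that the registry will report lower bilirubin-based scores as organ recovery. No sentence says so. The Liver Failure section itself speaks of removal and of bridging by detoxification. This stands.
- **Liver scores.** A reader might extend the point to MELD, PELD, CLIF, Maddrey and Lille as outcomes. Textbox 3 does not list these as changes, and they may serve as severity measures. This stands: only a later use of them as early change would raise the problem.
- **Cytokines and myoglobin.** A reader might add these too. Cytokines are listed as inflammatory biomarkers and not as organ function. Myoglobin is tracked for rhabdomyolysis, where its removal is the aim of treatment. Following a target analyte as device performance is legitimate. This stands.
- **Left to the analysis plan.** The article refers to a statistical analysis plan that is not shown, and the choice of SOFA version may sit there. This carries part of the weight. Even so, the article itself fixes the measure and its time points, sets analysis principles and offers no separation.
- **Magnitude.** The registry is unselected, and medians of 3 to 20 mg/dL describe jaundiced cohorts. This stands, so the larger figures must not be read as registry-wide.
- **Other outcomes.** Subscores, organ-support days, length of stay and mortality up to day 90 are collected, so the registry does not depend on total SOFA. That limits the damage and makes the correction easy, but leaves early total SOFA as a mixed measure.

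**Conclusion.** The point holds for SOFA change during therapy and within 24 hours after it. The hepatic subscore, and through it the total, mixes adsorption with organ function, and the published text provides no separation. The size is uncertain: about 0.07 to 0.28 points at an assumed median of 0.8 mg/dL with 10–50% net removal, and 0.26 to 0.85 points in assumed jaundiced cohorts with 30–50% net removal. Both ranges rest on the standard SOFA cut-offs, a lognormal distribution with log-SD 0.6, and assumed removal fractions. The mean effect is below one point, but it runs in one direction and is concentrated in patients just above a cut-off, which matters most where response is defined by a SOFA change. The documents do not support a claim that removal will be presented as recovery, or that all collected liver scores and biomarkers are misused.

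**What to change.** In Data Capture and Outcomes and in Analysis and Statistical Methods (or the analysis plan), for changes during therapy and within 24 hours after it:

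1. Report SOFA without the hepatic subscore alongside the full total and each subscore.
2. Use the non-hepatic total in any responder or predictor analysis.
3. Label early falls in bilirubin, bile acids and any bilirubin-containing liver score as marker removal, not liver function.

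Two apparent alternatives are not recommended. Restricting liver scores to discharge would select survivors in conditions that the article describes as having very high mortality, and Lille needs a follow-up bilirubin by definition. Coagulation results as a substitute for liver function are confounded by the anticoagulation, blood products and plasma exchange that Textbox 3 also records.

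Cost: a sentence of text and a few table rows from subscores already listed for collection. The non-hepatic total is not directly comparable with published SOFA totals, which is why the full total is kept beside it.
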